#### Confounding factors

2.5.3

The protocol prohibits a combination of anti-OP drug.

#### Discontinuation criteria

2.5.4

a Subjects who have experienced a severe adverse reaction or event that prevents them from continuing to be under treatment;

b Subjects who develop severe comorbidity or other systemic serious medical conditions during the trial and are unable to persist;

c Subjects who have poor compliance and do not cooperate with the relevant treatment despite repeated explanations;

d Subjects who request to withdraw from the study on their own;

e Subjects who take other drugs privately during the treatment period, which may interfere with the study results;

f The patient lost during the follow-up period for various reasons.

### Randomization and allocation concealment

2.6

First, we intend to generate a random number table from 1 to 120 in Excel and made random number cards. Secondly, we paln to mark the random numbers and groups on the cards following the correspondence principle, putting them in opaque envelopes and disrupting the order of the envelopes. Then, all envelopes are to be placed into a box. Outpatients who met the inclusion criteria in the Rehabilitation Department of Shenzhen Bao’an Hospital of Traditional Chinese Medicine can draw one envelope from the box in the order in which they are treated. Individuals receiving an envelope with a number less than or equal to 96 will be eligible to participate in our study. We intend to use Excel to generate a table of random numbers from 1 to 96. Subjects from 1 to 32 are assigned to follow Catgut embedding in acupoints at the CEA group. Subjects from 33 to 65 are designated for the combined treatment group (rTMS combined with the CEA group), while the remaining 32 are allocated to the rTMS group. Patients are randomly divided into three groups, each comprising 32 individuals. Each group is scheduled to receive the corresponding treatment measures.

### Blinding

2.7

A professional acupuncturist will independently operate the participants in the CEA group, while an independent professional physician is tasked with treating the rTMS group. The patients in the combined treatment group are to be treated by two trained physicians who collaborate to complete the two intervention plans. The treatment therapists of each group could not obtain specific treatment modes for the other two groups. Upon completing the treatments for the three groups, they are to inform the evaluator of the group code corresponding to the participant. The evaluator is to conduct scale testing on the participants and collect and record data in the case report forms, without access to information about the patients’ group allocations. The researchers responsible for statistical calculations are to remain blinded to the group allocations, having access only to the group codes.

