#### Clinical manifestation

2.11.1

SF-MPQ and OSS will be measured every four weeks for 5 months. All evaluation indicators will be assessed at six time points: baseline, mid-treatment (4 and 8 weeks of treatment), post-treatment (12 weeks), and 1 month and 2 months after the treatments.

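### Therapists give the outcome evaluator each participant's group code at the end of treatment, which weakens the assessor blinding claimed in the same paragraph

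*Protocol article*

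**What the plan says.** Section 2.7 assigns therapists by arm: an acupuncturist for the CEA group, a separate physician for the rTMS group, and two physicians together for the combined group. Masking between them covers only the other arms: "The treatment therapists of each group could not obtain specific treatment modes for the other two groups". Each therapist therefore knows the treatment given in their own arm.

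The next sentence sets the handover: "Upon completing the treatments for the three groups, they are to inform the evaluator of the group code corresponding to the participant". The evaluator's job follows: "The evaluator is to conduct scale testing on the participants and collect and record data in the case report forms", and this is to be done "without access to information about the patients’ group allocations". The paragraph closes with the statisticians, who "are to remain blinded to the group allocations, having access only to the group codes".

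Section 2.11.1 sets six assessment times for the SF-MPQ and OSS: "baseline, mid-treatment (4 and 8 weeks of treatment), post-treatment (12 weeks") and then 1 and 2 months after treatment. Table 1 in section 2.9.1 gives the MMSE and BDI-II the same schedule. Section 2.10.2 makes pain relief part of one category of the efficacy rating, which is a primary outcome.

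**The concern.** Participant-level group membership goes to the one person who is meant to have no allocation information, and it comes from people who know the treatment. The article does not define the code, call it a masked label or say who holds the key.

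No sham and no patient masking are described, and the treatments differ plainly (embedded sutures versus a magnetic coil). The evaluator is thus the main masking safeguard for ratings that pass through an observer. If the evaluator can group participants by arm, or guess the arm, expectations about the combined treatment can enter how a scale is given, prompted or recorded. The scales matter to the trial: section 2.8 bases the sample size on change in the SF-MPQ.

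**Working it through.** No test statistic or power figure is involved. The check sets the sentences beside the assessment schedule and counts who would be exposed.

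**1. Is the code needed?** Nothing in the descriptions of the SF-MPQ, OSS, MMSE or BDI-II requires a group label. A participant identifier is enough to administer a scale and complete the case report form.

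**2. What does a neutral code reveal?** There are three groups and 96 participants (section 2.6), so 96/3 = 32 per code. The number ranges printed there are slightly uneven: 1 to 32 is 32 numbers, 33 to 65 is 65 − 33 + 1 = 33, and the rest is 96 − 65 = 31. Hence about 32.

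- With a participant ID only, one explicit disclosure of treatment identifies 1 participant.
- With a shared code, one explicit disclosure identifies about 32.
- With two codes identified, the third follows by elimination, so all 96 are identified.

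This count holds for an explicit disclosure, not for every clue. A suture mark shows that CEA was given, but section 2.9.4 gives CEA to the combined arm too. A mark therefore leaves two of the three arms possible.

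**3. Does the source of the code add information?** Therapists are arm-specific. If the evaluator can tell who supplied the code, the supplier points to the arm even when the label is neutral. The article does not say whether the handover is in person or participant by participant, so this can happen but is not certain.

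**4. Which assessments come after the handover?** The timing phrase in section 2.7 can be read in three ways.

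| Reading | Assessments made after the code is known |
|---|---|
| As each participant finishes treatment, before the scales (sentence order) | Week 12, 1 month, 2 months: 3 of 6 |
| As each participant finishes treatment, after the week-12 scales | 1 month, 2 months: 2 of 6 |
| Once everyone in all three groups has finished treatment | At least the follow-ups of the last participants to finish |

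Follow-up runs 8 weeks beyond treatment, so no reading places the handover after the last assessment. A participant's baseline, week-4 and week-8 assessments come before that participant's own treatment ends and are untouched by this step on all three.

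**5. Which outcomes are open to observer influence?** Bone density is measured by DXA, and leptin, its receptor and norepinephrine are blood assays; these are not materially affected. In the efficacy rating, an increase in density alone gives the top category, and the middle one needs pain relief with no fall in density. As written, the pain judgement decides only where density has neither risen nor fallen. The article does not say how such a change is declared, so the number of participants concerned cannot be derived.

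**The case against.** The strongest reply is that the paragraph itself separates codes from allocations. The statisticians hold the codes and are still called blinded, and the evaluator is expressly said to have no allocation information. Read as a whole, the evaluator may be receiving nothing more than a masked label. This stands against the stronger inference a reader might draw, that the handover undoes assessor blinding: the documents do not show that the code is recognisable or that the evaluator has the key. It does not make the step harmless. A statistician with codes has no described contact with patients, whereas the evaluator meets them and receives the code from the treating side.

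A reader might also infer that the code is always known before the week-12 scales. Only sentence order supports that. The follow-up exposure does not depend on it.

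Third, several ratings are largely the patient's own. Participants mark the SF-MPQ visual scale themselves (section 2.11.1.1), and OSS symptoms are kept on diary cards before the doctor's review (Table 6). For these, unmasked patients are a main source of bias and withholding a code will not cure it. This stands, and it limits the benefit of the change.

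Last, a condensed article may leave code custody and staff instructions to the full protocol. That is fair, so their absence is not criticised here. The point rests on an instruction the article does state.

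**Conclusion.** The point holds as a weakness in a stated procedure, not as demonstrated unblinding. The evaluator receives an unneeded participant-level group code from therapists who know their own arm's treatment, beside a claim that the evaluator has no allocation information. The two sentences need to be reconciled.

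With participant-by-participant handover, the exposure is the two follow-up assessments, plus week 12 if sentence order is the order of events. With a single handover after all treatment has ended, it shrinks to the follow-ups of later finishers. The consequence of one explicit disclosure grows from 1 participant to about 32. The direction and size of any resulting bias cannot be estimated from the article.

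This assumes that the article's wording is the procedure to be followed and that the evaluator who receives the code also carries out the later assessments, as the text implies. The change should be made because it removes an avoidable route to detection bias at almost no cost.

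**What to change.** Replace the handover sentence in section 2.7 with three statements:

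- Therapists pass no group information to the evaluator at any time.
- The evaluator works at every visit, follow-up included, with a neutral participant ID. This must not be the allocation number from section 2.6, because those numbers map directly to arms.
- Masked group codes (A/B/C) go only to the statistician, after all assessments are complete and the data are locked.

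The cost is one rewritten sentence and a staff instruction, with no extra staff, visits or participants. Section 2.16 reports that recruitment is under way, so the instruction should be issued promptly. The report should still acknowledge that patients were not masked and that their own ratings may carry bias this change does not remove.

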### Sample size calculation

2.8

This randomized controlled study evaluates the effects of three methods on postmenopausal patients with OP. Bone mineral density (BMD), McGill Pain Questionnaire Short-Form (SF-MPQ), Osteoporosis Symptom Score (OSS), Mini-Mental State Examination (MMSE), and Beck Depression Inventory-II (BDI-II), serum leptin, leptin receptor, norepinephrine level will be used as evaluation indicators. According to the preliminary test data, it was calculated that after treatment, the SF-MPQ score (PRI total score) in the CEA group decreased by 17.23 ± 2.84, that in the rTMS group decreased by 16.41 ± 1.77, and that in the CEA combined with rTMS group decreased by 17.40 ± 2.17. The two-sided test value α = 0.05 was used. Test power 1-β = 0.95. Using G*Power3.1.9.7 software and single factor analysis of variance in the F test (27, 28), the required sample size of n = 87 cases was calculated, and the shedding rate was set at 10%. The total sample size was 96 cases, and the required sample size for each group was 32 cases.

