#### Study schedule

2.9.1

Baseline information on age, menopause age, weight, education, vital signs, and duration of illness will be collected and recorded (Table 1). Then, the primary outcomes will be the changes in BMD scores and total efficiency of Chinese Medicine Symptoms before and after treatment. Secondary outcomes will include the SF-MPQ, OSS, MMSE, and BDI-II every 4 weeks for 12 weeks of treatment and 8 weeks follow-up period. Adverse events that occur during the trial will be recorded. The leptin, leptin receptor, and norepinephrine levels of peripheral blood must be measured before and after treatment.

**Table 1 tab1:** Trial flow and schedule: enrollment, interventions, and assessments.

Research stage			Duration of treatment (weeks)				Follow-up period (weeks)	
Inclusion/exclusion criteria			0	4	8	12	4	8
Sign the informed consent form			√					
		General information	√	√	√	√		
		Previous medical history	√					
		Clinical symptoms and physical signs	√	√	√	√		
Physical examination		Tongue manifestation, pulse, manifestation, weight	√			√		
		Vital signs: T, BP, P, R.	√			√		
Security check		Electrocardiogram	√			√		
		Liver function	√			√		
		Renal function	√			√		
		Blood lipids	√			√		
Intervention		CEA						
		rTMS						
		CEA combined with rTMS						
Efficacy indicators	Primary outcome	①BMD	√			√			②Total efficiency of Chinese Medicine Symptoms	√			√		
		③SF-MPQ	√	√	√	√	√	√
		④OSS	√	√	√	√	√	√
	Secondary outcome	⑤Leptin	√			√		
		⑥Norepinephrine	√			√		
		⑦Leptin receptor	√			√		
		⑧MMSE	√	√	√	√	√	√
		⑨BDI-II	√	√	√	√	√	√
Blood sample collection			√			√		
Randomization			√					
General assessment	Clinical efficacy					√		
	Compliance assessment		√	√	√	√		
	Adverse event		√	√	√	√		
	Safety evaluation		√			√		

T, Temperature; BP, Blood Pressure; P, Pulse; R, Respiration; CEA, Catgut Embedding in Acupoints; rTMS, repetitive Transcranial Magnetic Stimulation; BMD, Bone Mineral Density; SF-MPQ, McGill Pain Questionnaire Short-Form; OSS, Osteoporosis Symptom Score; MMSE, Mini-Mental State Examination; BDI-II, Beck Depression Inventory-II.

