### Statistical analysis

2.14

The data will be recorded and checked for accuracy, and the data related to baseline and clinical symptoms will be statistically analyzed using SPSS 27.0 software. The *t*-test will be performed for customarily distributed measures that meet the chi-squared test, and the *t′*test will be conducted for standards that meet the normal distribution but do not meet the chi-squared test. Independent sample *t*-tests are used between two groups, and paired sample *t*-tests will be used for pre-treatment and post-treatment comparisons within groups. Non-normally distributed measures are described by “median (interquartile range)” [*M (IQR)*], and non-parametric tests will be performed. *The Mann–Whitney U* test will compare two independent samples, and the *Wilcoxon Z* test will be used for pre-and post-treatment-comparisons. The scale scores at more than three of these time points are compared using repeated measures *ANOVA*. Correlations will be expressed as correlation coefficients (*r*). Correlations between the two measurement variables will be analyzed by Pearson correlation analysis if they conform to a normal distribution and Spearman analysis if they do not obey a normal distribution. Given that our study defines two primary outcomes, a Bonferroni correction will be applied, thus adjusting the significance level for individual outcome analyzes to *α*/2 to control the overall type I error rate, setting *α* = 0.05 (39).

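### The pilot figures in the sample size section give about 32% power at n = 87, not the stated 95%, and the calculation does not cover the two primary outcomes

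*Protocol article*

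**What the plan says.** Section 2.8 (Sample size calculation) of the protocol article prints its inputs. From preliminary data, "the SF-MPQ score (PRI total score) in the CEA group decreased by 17.23 ± 2.84"; the corresponding figures are 16.41 ± 1.77 for rTMS alone and 17.40 ± 2.17 for the combination. It adds that "The two-sided test value α = 0.05 was used", sets power at 0.95, and names G*Power and a single-factor ANOVA F test. The result is that "the required sample size of n = 87 cases was calculated, and the shedding rate was set at 10" per cent, which leads to 96 patients, 32 per group. No effect size f and no common SD are shown.

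On the status of SF-MPQ, section 2.9.1 (Study schedule) says that "Secondary outcomes will include the SF-MPQ, OSS, MMSE, and BDI-II" at four-week intervals. The abstract and section 2.11 also place SF-MPQ among the secondary outcomes. The primary outcomes named in the text are BMD and total efficiency of Chinese Medicine Symptoms. Section 2.14 (Statistical analysis) states: "Given that our study defines two primary outcomes, a Bonferroni correction will be applied", which puts each primary outcome at alpha 0.05 / 2 = 0.025.

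**The concern.** The three pilot means span less than one point (16.41 to 17.40), while the smallest of the three SDs is 1.77. Differences that small against that much spread should not be detectable with 95% power in 29 patients per group.

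The 95% figure is the article's only statement of what the trial can detect. If it is wrong, readers are misinformed about the chance of finding the differences that the sponsor's own pilot suggests. The figure also comes from an outcome, and an alpha, that are not those of the primary analysis. Even a correct calculation on SF-MPQ would leave the primary outcomes without a power statement.

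**Working it through.** **Inputs** (all from section 2.8): mean decreases 17.23, 16.41, 17.40; SDs 2.84, 1.77, 2.17; alpha 0.05; power 0.95; three equal groups; omnibus one-way ANOVA.

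**Step 1. Effect size.**
- Grand mean = (17.23 + 16.41 + 17.40) / 3 = 17.013.
- SD of the means (divisor 3) = √[(0.217² + 0.603² + 0.387²) / 3] = √0.1868 = 0.432.
- Pooled SD = √[(2.84² + 1.77² + 2.17²) / 3] = √5.302 = 2.303. Pilot group sizes are not given, so equal weights are assumed; step 4 removes that assumption.
- f = 0.432 / 2.303 = 0.188.

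**Step 2. Attempt to reproduce 87.** Power comes from the noncentral F distribution with 2 and N − 3 degrees of freedom and noncentrality λ = N f².
- N = 87: λ = 3.07, power 31.7%. A simulation with the three unequal SDs gives 31.9%.
- N = 96: λ = 3.38, power 34.8%.
- 95% power: N = 444 (148 per group).

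The stated 87 is not reproduced; the requirement is about five times larger (444 / 87 = 5.1).

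**Step 3. What does return 87.** With a within-group SD of 1, f = 0.432 / 1 = 0.432. Power is then 95.3% at N = 87 and 94.6% at N = 84, so the answer is exactly 87. Only SDs of about 0.99 to 1.01 do this. No listed SD is near 1.

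**Step 4. Do other readings rescue it?**

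| Reading | f | N for 95% power | Power at 87 |
|---|---|---|---|
| Pooled SD 2.303 | 0.188 | 444 | 32% |
| Arithmetic mean SD 2.26 | 0.191 | 426 | 33% |
| Smallest SD, 1.77, for all groups | 0.244 | 264 | 50% |
| SD 2.17 for all groups | 0.199 | 393 | 35% |
| Largest SD, 2.84, for all groups | 0.152 | 672 | 22% |
| Divisor k − 1 for the SD of the means, pooled SD | 0.230 | 297 | 45% |

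Any weighted pooled SD must lie between 1.77 and 2.84, so unknown pilot group sizes cannot change the conclusion. A lower power target does not help either: with the pooled SD, N = 363 for 90% and 279 for 80%. Reading 87 as a per-group number (261 in total) gives 77.5%.

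**Step 5. What can be said about BMD.** Section 2.14 plans two-group t-tests, and BMD is measured once before and once after treatment. With 29 evaluable per arm (87 / 3), 80% power and two-sided alpha 0.025:
- Normal approximation: (2.241 + 0.842) × √(2/29) = 0.81 SD. The t distribution with 56 degrees of freedom raises this to 0.83 SD.
- If alpha is also split over three pairwise comparisons (0.025 / 3 = 0.0083): (2.638 + 0.842) × √(2/29) = 0.91 SD, or 0.94 SD with the t distribution.

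The article gives no SD for the 12-week change in BMD, so these values cannot be turned into g/cm² here. It gives no assumed response rate for total efficiency, so no detectable difference in proportions can be computed.

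**The case against.** **SF-MPQ is measured six times.** Section 2.14 plans repeated measures ANOVA for scale scores at several time points, which can be more powerful than a single comparison. This stands as a limit on scope: 32% is the power of the one-way ANOVA named in section 2.8, not necessarily of the eventual SF-MPQ analysis. It does not rescue 87. Repeated-measures settings with 2, 4 or 6 time points and a correlation of 0 or 0.5 gave totals from 78 to 333, none equal to 87, and the article states no correlation.

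**Table 1 may place SF-MPQ in the primary block.** As extracted, SF-MPQ and OSS appear before the secondary outcome label. The layout is ambiguous, but the abstract, sections 2.9.1 and 2.11, and the count of two primary outcomes in section 2.14 all point to secondary. If SF-MPQ were primary, the arithmetic would fail all the same.

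**The cause is not documented.** A reader might infer from step 3 that an SD of 1 was entered in the software. The exact match suggests this, but no f or common SD is shown, so it is not proven. The finding does not depend on it.

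**Dropout.** A reader might add that the 10% loss was applied wrongly: 87 × 1.1 = 95.7, against 87 / 0.9 = 96.7. That is 96 or 97 patients, a rounding matter, and is no part of this point.

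**Conclusion.** The claim of 95% power with n = 87 is wrong on the article's own inputs. For the named test, power is about 32% with 87 evaluable patients and 35% with 96; 95% power needs about 444. The most favourable single listed SD still gives only 50% power and a required total of 264. These results rest on the printed means and SDs, equal groups and the single-time-point one-way ANOVA.

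Separately, the calculation uses SF-MPQ at alpha 0.05, so it does not support the two primary outcomes at alpha 0.025, and no other section states their power.

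Two stronger readings are not supported. A reader might infer that a null result will be taken as equal efficacy of the three treatments. No section plans an equivalence or non-inferiority reading, and the stated hypothesis is synergy of the combination. A reader might also carry the 32%, or a detectable ANOVA effect size, over to the primary outcomes. Total efficiency is a responder rate, and BMD falls under the two-group tests of section 2.14, so neither is described by an omnibus f.

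**What to change.** Keep 96 patients and reword section 2.8:

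1. Withdraw the 95% power claim. State that about 87 evaluable patients give about 32% power for the pilot SF-MPQ differences under the one-way ANOVA named there.
2. For BMD, state the detectable pairwise difference under the planned two-group t-test: about 0.83 SD at 80% power with 29 per arm and alpha 0.025, or about 0.94 SD if alpha is also split over three pairwise comparisons. Translate it into g/cm² with the sponsor's own SD of the 12-week change.
3. For total efficiency, state the detectable difference in responder proportions at alpha 0.025, using the sponsor's own assumed response rate.
4. Make the layout of Table 1 agree with the text on the status of SF-MPQ.

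The cost is wording and a short calculation from data that the sponsor would have to supply. No extra patients are proposed. The downside is that the stated power becomes much less favourable.

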**Method:**

This trial is a prospective and randomized controlled trial. 96 PMOP participants will be randomized in a 1:1:1 ratio into a CEA group, an rTMS group, or a combined one. Participants will receive CEA, rTMS, or combined therapy for 3 months with 8 weeks of follow-up. The primary outcomes will be the changes in Bone Mineral Density scores, total efficiency of Chinese Medicine Symptoms before and after treatment. Secondary outcomes include the McGill Pain Questionnaire Short-Form, Osteoporosis Symptom Score, Mini-Mental State Examination, and Beck Depression Inventory-II. The leptin, leptin receptor, and norepinephrine levels of peripheral blood must be measured before and after treatment. Adverse events that occur during the trial will be recorded.

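### The sample size of 87 does not follow from the means and SDs printed in section 2.8: with those figures the stated ANOVA has about 32% power, not 95%, and 95% would need 444 women

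*Protocol article*

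**What the plan says.** Section 2.8 (Sample size calculation) takes its assumptions from preliminary data on the SF-MPQ total score:

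- CEA: "the SF-MPQ score (PRI total score) in the CEA group decreased by 17.23 ± 2.84"
- rTMS: "that in the rTMS group decreased by 16.41 ± 1.77"
- Combined: "that in the CEA combined with rTMS group decreased by 17.40 ± 2.17"

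The design settings are "The two-sided test value α = 0.05 was used" and "Test power 1-β = 0.95". The method is given as "Using G*Power3.1.9.7 software and single factor analysis of variance in the F test". The result is that "the required sample size of n = 87 cases was calculated, and the shedding rate was set at 10" per cent, which is then raised to 96, or 32 per arm. The abstract gives the allocation: "96 PMOP participants will be randomized in a 1:1:1 ratio into a CEA group, an rTMS group, or a combined one". The section states neither the effect size f nor the common SD that was entered.

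**The concern.** A one-way ANOVA calculation depends on how far the group means differ relative to the spread within groups. Here the largest difference between means is 17.40 − 16.41 = 0.99 points, while the printed SDs run from 1.77 to 2.84. A difference of less than half a typical SD, across three arms of 29, cannot plausibly give 95% power.

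The 95% power and the figure of 87 are the only quantitative grounds offered for enrolling 96 women. If they are wrong, the trial's size has no valid justification. A reader who trusts the 95% would also give a non-significant comparison of the arms far more weight than it deserves.

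**Working it through.** **Inputs** (section 2.8; allocation from the abstract): means 17.23, 16.41, 17.40; SDs 2.84, 1.77, 2.17; alpha 0.05; power 0.95; three equal groups; omnibus F test. Calling the test two-sided changes nothing, because the omnibus F test has a single rejection region.

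**Method.** f = (SD of the group means) / (common within-group SD). Power is the upper tail of the noncentral F distribution with 2 and N − 3 degrees of freedom and noncentrality λ = N f². The required N is the smallest multiple of 3 that reaches the target.

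**Step 1: spread of the means.** Grand mean = (17.23 + 16.41 + 17.40)/3 = 17.0133. Squared deviations are 0.0469, 0.3640 and 0.1495, total about 0.5605. SD of the means = √(0.5605/3) = 0.4322.

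**Step 2: reproducing 87.** With a within-group SD of 1, f = 0.4322. Power is 0.946 at N = 84 and 0.953 at N = 87, so 87 is exactly the smallest balanced total. Working backwards, a common SD returns 87 only if it lies between about 0.989 and 1.008. The final 96 follows as 87 × 1.1 = 95.7, rounded up.

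**Step 3: the printed SDs.** Pooled SD = √((2.84² + 1.77² + 2.17²)/3) = √(15.9074/3) = 2.3027. f = 0.4322/2.3027 = 0.1877. N for 95% power is 444 (0.951; 441 falls just short at 0.9499). For 90% it is 363 and for 80% it is 279.

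**Step 4: sensitivity to the choice of SD.**

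| Common SD | f | N for 95% power | Power at 87 | Power at 96 |
|---|---|---|---|---|
| 1.77 (smallest printed) | 0.244 | 264 | 50.4% | 54.8% |
| 2.17 (middle printed) | 0.199 | 393 | 35.3% | 38.7% |
| 2.26 (mean of the three) | 0.191 | 426 | 32.8% | 36.0% |
| 2.303 (pooled) | 0.188 | 444 | 31.8% | 34.8% |
| 2.84 (largest printed) | 0.152 | 672 | 22.0% | 24.0% |
| 1 (not printed) | 0.432 | 87 | 95.3% | 97.0% |

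A simulation of the ordinary ANOVA with the three unequal SDs gave 31.7% power at 29 per arm and 35.2% at 32 per arm, so the unequal spread does not explain the gap.

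**Step 5: other routes to 87.** With the printed SDs, alpha 0.10 gives 372; divisor 2 instead of 3 for the SD of the means gives 297; treating the SDs as variances gives 192. Pairwise t-tests at 95% power need 104 to 5744 per group. Repeated-measures versions, with 2, 4 or 6 measurements and correlation 0 or 0.5, gave totals from 60 to 333, none of them 87. The nearest miss enters both the SD of the means and the mean SD as if they were variances; that gives 84.

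**Step 6: what 87 can detect.** At N = 87, 95% power requires f = 0.429, which is 0.429/0.1877 = 2.3 times the pilot value. If the three means keep the pilot pattern, the rTMS-to-combined difference would have to be 0.99 × 2.29 ≈ 2.3 points.

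**The case against.** The arithmetic is not in dispute. The other side can fairly make four points.

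- **The cause is inferred.** Section 2.8 does not say which SD or f was entered. An f between about 0.429 and 0.437 typed in directly would also give 87. This stands: SD = 1 is the likely explanation, not an established one. The mismatch between printed inputs and printed result does not depend on it. Nor does it help that the ± values are not labelled as SDs: read as standard errors, they would imply larger SDs and a larger shortfall.
- **The 32% belongs to a test the analysis section does not name.** Section 2.14 plans two-group tests and repeated-measures ANOVA, and SF-MPQ is measured at six time points. This also stands. The 32% is the power of the test in section 2.8, not of every comparison the trial will make.
- **SF-MPQ is a secondary outcome** in the abstract and section 2.11, so the shortfall says nothing direct about power for BMD or the overall effective rate. True, but section 2.8 offers no other calculation, so the trial's size rests on this one.
- **Misreading of a null result is a prediction.** No passage commits the investigators to treating non-significance as equivalence. That is right; the firm consequence is that the stated justification for 96 women is invalid.

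That a journal article condenses a fuller protocol is no answer here: nothing is missing, and the printed figures disagree with each other.

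**Conclusion.** The concern holds. On the protocol's own figures, the one-way ANOVA at alpha 0.05 has about 32% power with 87 evaluable women and about 35% with 96, against the 95% claimed. Reaching 95% would take 444, about five times the stated 87. No printed SD, alone or combined, brings the requirement below 264.

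This assumes that the ± values are SDs, that the arms are equal in size and that the test is the omnibus F test named in section 2.8. That the within-group SD was left at 1 is an inference from the exact match at 87. The finding concerns only this calculation; which outcome, test or alpha should drive the sample size is a separate question.

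**What to change.** Correct section 2.8 while keeping the planned size:

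- State f = 0.188, with the SD of the means (0.432) and pooled SD (2.303) behind it.
- State that 87 evaluable women give about 32% power, and 96 about 35%, for the omnibus ANOVA.
- Delete the claims of 95% power and of a required n of 87.
- Report what 87 women can detect with 95% power: f of about 0.43, or about 2.3 points between rTMS and combined if the means keep the pilot pattern.

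If a different f or SD was deliberately used, state and justify it instead. Presenting the SF-MPQ arm comparisons as estimates with confidence intervals would suit the lower power, but the correction does not depend on it.

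The cost is one rewritten paragraph and a much less favourable power statement, with no extra patients. Section 2.16 says version 1.0 is already recruiting, so this is an amendment to a live protocol and should be made before any results are seen.
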